### Randomization, allocation concealment, and partly double-blind

2.8

Third parties not involved in the study will use Excel 2013 software (Microsoft Corporation, Redmond, WA) to generate 90 independent random numbers and divide them by 3. The rest will be 1 in group A, 2 in group A, and 0 in group C. A, B, and C are defined as Chinese medicine group, placebo + diet group, Chinese medicine + diet group. If the enrolled patients fall off, the total number of enrolled patients exceeds 90, and they will be randomly grouped again according to needs. Patient serial numbers will be generated in the order of enrollment. When distributing medicines, neither the doctor nor the patient can know what kind of medicine. The drug number information will be retained, encapsulated, and stored in an opaque envelope, and kept by a third party. When the patient is enrolled, the envelope based on their serial number will be delivered to the researcher. After the trial, the third party will expose blindness. Because dietary intervention is a set of dietary principles rather than specific foods, it is difficult to be blinded, so only drugs are double-blind to reduce information bias.

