### Study design

2.2

The protocol was drafted using the SPIRIT guidelines and the results will be reported following the checklist of the Consolidated Standards of Reporting Trials statement (see Supplementary Table 1). All participants will be informed of the purpose of the study and obtain their informed consent before participating in this parallel group study. According to the inclusion and exclusion criteria, a total of 90 patients with functional constipation are expected to be recruited. Then they were randomly assigned to the Chinese medicine group (group A), placebo + diet group (group B), Chinese medicine + diet group (group C) at the ratio of 1: 1: 1. The patient filled out the case report form (CRF) after confirming enrollment, and the researchers recorded the patient's symptoms, bowel movements, etc., on day 14 (phone follow-up) and day 28. Interventions were provided to subjects based on the enrollment number, but neither the patient nor the investigator knew whether the patient was receiving drug or placebo. The entire study design is shown in the figure (see Fig. 1). A SPIRIT figure for the schedule of enrolment, interventions, and assessments is also presented (see Fig. 2).

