### Sample size

2.5

Because there is still insufficient clinical evidence, this study is a small sample exploratory study with a total sample size of 90 people (each treatment group has 30 samples).

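### The printed allocation rule never assigns group B; once corrected, it gives 1:1:1 only in expectation, and the rule for extra patients is left open

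*Protocol article*

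**What the plan says.** Section 2.2 (Study design) of the protocol article names three groups, A (Chinese medicine), B (placebo + diet) and C (Chinese medicine + diet), and ends the list with "Chinese medicine + diet group (group C) at the ratio of 1: 1: 1". Section 2.5 (Sample size) sets a total of 90 and adds that "each treatment group has 30 samples".

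Section 2.8 (Randomization) says how the list is made. A third party will "generate 90 independent random numbers and divide them by 3", and the remainder decides the group: "The rest will be 1 in group A, 2 in group A, and 0 in group C". The next sentence reads "A, B, and C are defined as Chinese medicine group, placebo + diet group, Chinese medicine + diet group". No blocking or fixed count per arm is described.

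On dropouts, the same section says that "the total number of enrolled patients exceeds 90, and they will be randomly grouped again according to needs".

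**The concern.** Division by 3 leaves only the remainders 0, 1 and 2. The printed rule sends two of them to A, one to C and none to B, so it cannot produce the three-arm design stated elsewhere in the article. At stake is the comparison of C with B, the only one in which diet is the same in both arms and the herbal powder differs from placebo.

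Two lesser matters sit in the same section. Independent random numbers do not fix arm sizes, although section 2.5 states 30 per group without qualification. And the sentence on extra patients does not define the needs it refers to. One possible reading is that replacements go to whichever arm has lost patients, in which case later assignments would depend on what happened after randomisation.

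**Working it through.** **Inputs.** N = 90 and 30 per arm (section 2.5); ratio 1:1:1 (section 2.2); independent numbers, remainder modulo 3, and the printed mapping (section 2.8).

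**1. The plan's own figure.** 90 × 1/3 = 30 per arm. The ratio and the total agree with each other.

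**2. The rule as printed.** Each remainder has probability 1/3.
- A (remainders 1 and 2): 2/3, expected 90 × 2/3 = 60.
- B (no remainder): 0, expected 0.
- C (remainder 0): 1/3, expected 90 × 1/3 = 30.

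The split 30/30/30 is impossible. With A distributed as binomial(90, 2/3), P(A ≥ 50) = 98.9%.

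**3. The rule with remainder 2 read as B, independent numbers.** Arm sizes follow a trinomial(90; 1/3, 1/3, 1/3).
- Expected size of each arm: 30.
- SD of one arm: √(90 × 1/3 × 2/3) = √20 = 4.47. Approximate 95% range: 30 ± 1.96 × 4.47 = 21.2 to 38.8.
- P(exactly 30/30/30) = 90!/(30!³ × 3⁹⁰) = 0.0091, about 0.9%.
- Summing the exact distribution: P(every arm within 2 of 30) = 16.0%; P(smallest arm ≤ 25) = 45.8%; P(largest minus smallest ≥ 10) = 43.6%; expected gap between largest and smallest arm = 9.3.

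**4. What that imbalance costs.** With equal outcome variances, the variance of a difference between two arms is proportional to 1/n₁ + 1/n₂.
- 25 v 35 against 30 v 30: (1/25 + 1/35)/(2/30) = 0.06857/0.06667 = 1.029. The standard error rises by about 1.4%.
- 21 v 39 against 30 v 30: (1/21 + 1/39)/(2/30) = 0.07326/0.06667 = 1.099. The standard error rises by about 5%.

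**5. The rule with remainder 2 read as B, numbers 1 to 90 in random order.** Each remainder occurs exactly 30 times, so the split is 30/30/30. Section 2.8 calls the numbers independent, which speaks against this reading, but it shows that a small change to the method secures the stated totals.

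**6. Extra patients.** Section 2.8 says that these patients are grouped at random, and that this is done as needed. It does not say whether the need refers to how many patients are added or to which arm is short. No arithmetic settles this; the text allows both.

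**The case against.** The strongest reply is that the second A is a one-letter slip. The next sentence of section 2.8 defines A, B and C in order, section 2.2 lists the same three arms, and section 2.7 describes how the placebo is made. A third party would very likely notice. This stands as an explanation, and it means that 60/0/30 measures the printed text and does not forecast the trial. It does not remove the error: this is the only description of sequence generation in the article, and it contradicts the stated design.

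A reader might infer that neither random numbers nor refilling can give 1:1:1 with 30 per arm. The documents do not support that. Corrected, independent numbers do give 1:1:1 in expectation, and refilling could bring the arms to 30. The accurate statement is that 30 per arm is not ensured.

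A reader might also infer that unequal arms bias the comparison. They do not: unrestricted randomisation is valid, and step 4 shows a small loss of precision. Section 2.5 rests on no power calculation, so no stated power is lost.

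Finally, a reader might infer that replacements will be steered to depleted arms. The text says "they will be randomly grouped again according to needs", so random grouping is stated and steering is only one possible reading. The third party also holds opaque envelopes that are released by serial number, so predictable late assignments are not shown. What remains is that the rule is undefined.

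Blocking is not a free remedy either. Section 2.8 accepts that diet cannot be blinded, and only A has no diet intervention, so group A is visible. In a block of three, two diet patients reveal that the third is A.

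**Conclusion.** The mapping in section 2.8 is wrong as printed and must be corrected: it gives B a probability of zero and an expected 60/0/30, against 1:1:1 and 30 per group. This needs no assumption beyond equally likely remainders.

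The other two parts are smaller. Assuming remainder 2 is meant for B and the numbers are independent, 30 per arm is an expectation, with an SD of 4.5 per arm and about a 0.9% chance of exact balance. That is a mismatch between a stated number and the method meant to produce it. It is not a source of bias, and for a 25 v 35 split it adds about 1.4% to the standard error. The rule for extra patients is unclear; the documents establish no bias from it, and its size cannot be calculated from them.

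**What to change.** 1. In section 2.8, print the mapping as remainder 1 = A, 2 = B, 0 = C. This changes one letter. If a list has already been generated, the third party should confirm that it contains group B.
2. Choose one of two courses for arm sizes. Either describe 30 per group in section 2.5 as the expected number, which costs only wording; or have the third party use a list with fixed totals, for example the numbers 1 to 90 in random order before taking remainders, or larger blocks of concealed, varying size. The second course means regenerating one list. Because diet status shows who is in A, small blocks are partly predictable, and the last places on any list with fixed totals can be too; block sizes and running counts should therefore stay with the third party.
3. Replace the sentence on extra patients. State that the concealed list is prepared in advance with spare numbers beyond 90, and that any extra patient takes the next unused number regardless of arm.
4. State in section 2.8 that patients who drop out stay in the intention-to-treat set under their assigned arm. Section 2.14 already commits to intention-to-treat analysis of randomised patients with at least one assessment, baseline included, so this only removes doubt about whether a replacement displaces the original patient.

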### Emergency unblinding

2.9

In case of any serious adverse events or emergency, the researcher will report to the supervisor and the main researcher to decide whether to open the emergency letter. Once opened, the case will be treated as exfoliated, excluded from the efficacy analysis, but will remain included in the adverse reaction analysis. Details of the unblinding cause, date, treatment situation, and results will be reported in the CRF and will be signed by the administrator.

### Quality control

2.10

Participants’ diet quality (DQ) will be assessed at the baseline and after the intervention. The foods involved are in LVD content.

### Data collection

2.11

#### Baseline information

2.11.1

Baseline information will include demographic data and clinical data from the participants. Demographic data includes gender, age, height, weight, nationality, occupation, and education level, etc. Clinical data includes past medical history, drug allergy history, the history of medications used to treat or induce constipation, dietary habits in the past year (see Supplementary Table 1), the primary outcome, and secondary outcomes.

#### Primary outcome

2.11.2

The number of CSBM per week is the primary outcome. It is effective when the number before the intervention subtracted from the number after the intervention is more than or equal to 1.

#### Secondary outcomes

2.11.3

Constipation-related symptom rating scale: The scale for constipation-related symptoms is used for investigating the degree and frequency of symptoms mentioned in Roman IV diagnostic criteria for FC. The degree of discomfort is assessed by visual analog scale, in which 0 represents no discomfort and 10 represents very strong discomfort. The final scores are obtained with the multiplication of the 2 and then divided by the average number of defecations per week (see Supplementary Table 2). Percent improvement will be calculated as follows: 

Recovery means symptoms disappeared; Marked improvement means percent improvement is more than or equal to 80%; Progress means percent improvement is more than or equal to 50% but less than 80%; Ineffective means percent improvement is less than 50%.

Traditional Chinese medicine syndrome scale (TCMSS): The TCMSS is established by collecting information about effects of relevant syndromes of TCM constipation, which are assigned 0, 1, 2, and 3 points representing normal, mild, moderate, and severe degrees, respectively. Normal refers to the absence of this syndrome, mild refers to a slight impact on life, moderate means a significant impact on life, and severe refers to the serious impact on life (see Supplementary Table 3). Nimodipine method is used for evaluating the effects of relevant syndromes of TCM constipation. 

Symptoms, signs disappeared or basically disappeared and syndrome integral reduced more than or equal to 95% is considered clinical cure; Significantly effective means that symptoms, signs significantly have improved, and syndrome integral has reduced more than or equal to 70%; Effective means that symptoms, signs have improved and syndrome integral has reduced more than or equal to 30%; Ineffective means that symptoms, signs have no improved or have even aggravated and syndrome score has reduced less than 30%.

Forty-eight hours GITT: 48-hour GITT is a simple method for evaluating the function of gastrointestinal motility. The barium residue rate is the ratio of the number of barium remaining in the body 48 hours after swallowing 20 barium bars with a standard meal. Higher residue rate indicates the worse gastrointestinal transport function. The parameters include barium excretion rate after 48 hours, residue rate above rectosigmoid colon and residue rate within rectosigmoid colon. The barium excretion rate in normal people is more than or equal to 90%.

HRAM: HRAM is used to estimate the function of anal sphincter, rectal sensation, and anorectal reflex for diagnosing the defecation disorder constipation. The parameters include mean pressure of resting anal sphincter, maximum contraction pressure of resting anal sphincter, anal relaxation rate during analog defecation, first sensory value, defecation sensory value, and maximum tolerance.

BSFS: The Bristol stool score is used to assess fecal traits under the naked eye. 1 point: scattered hard lumps, like nuts; 2 points: sausage-like, but agglomerate; 3 points: sausage-like, but with cracks on the surface; 4 points: sausage-like or snake-like, smooth, and soft; 5 points: soft balls, clear edges; 6 points: unclear edges, mushy stools; 7 points: watery, no solids.

PAC-QOL: The quality of life assessment scale for patients with constipation includes 4 parts, including physiological, psychological, constipation's impact on life and treatment satisfaction, a total of 28 items, using Linker 5 grade. The higher the total score, the lower the quality of life, which means the more dissatisfied with the current state of life (see Supplementary Table 4).

PAC-SYM: The symptom self-assessment scale for patients with constipation includes 3 dimensions (abdominal symptoms, rectal symptoms, and stool symptoms) and 12 items. The Linker 5 scale is used. The higher the score, the more severe the constipation symptoms (see Supplementary Table 5).

F-SCFAs: Detection of short-chain fatty acids in feces contains acetic acid, propionic acid, butyric acid, isobutyric acid, valeric acid, isovaleric acid, and caproic acid. Feces samples were collected before and after the intervention and stored in the −80°C refrigerator in the biological sample bank of the China-Japan Friendship Hospital. Inspection and analysis after the test.

#### Safety outcomes

2.11.4

Safety parameters include AEs and laboratory examinations (BR, LKF).

#### DQ and compliance measures

2.11.5

After the test, the proportion of qualified diets and the frequency of various food intakes will be calculated. The diet intervention group should strictly follow the requirements of light vegetarian diet, while the nondiet intervention group does not need to observe the light vegetarian diet. Dietary compliance rate (DCR) means the ratio of qualified meals to total meals times 100. When DCR is greater than or equal to 80%, high compliance is achieved, while low DCR is less than 80%.

### Adverse event

2.12

Adverse events refer to the negative effects caused by the intervention. During the trial, any abnormal reactions of the participants will be reported to the researchers. The time of onset, symptoms, degree, duration, and mitigation measures will be recorded in the CRF.

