### Planned statistical analysis

2.14

Continuous variables will be described as the mean ± standard deviation, median, or interquartile range. The number of cases, frequency, the rate, and the constituent ratio will be described by categorical variables. Variance analysis will be used for continuous variables in the baseline data having normal distribution and same variance. Wilcoxon rank sum test or Kruskal–Wallis H test will be used for the comparison of differences between groups that are not normally distributed or have uneven variance. Categorical variables will be tested by *χ*^2^ test or Fisher exact test. Wilcoxon rank sum test or Kruskal–Wallis H test will be used for the number of CSBM per week in primary outcome. *χ*^2^ test or Fisher exact test will be used for percent improvement of each symptom scale score in secondary outcome indicators. The result of 48-hour GITT will be analyzed using *χ*^2^ or Fisher test. Wilcoxon rank sum test or Kruskal–Wallis H test will be used for measurement data in HRAM, while *χ*^2^ test or Fisher exact test will be used for counting data. Safety, dietary quality, compliance indicators will be tested by *χ*^2^ test or Fisher exact test. Complying with the intent-to-treat and per-protocol principle, all data of the patients randomized and at least 1 assessment (include baseline assessment) will be analyzed. For dropouts and terminations, their missing data will be obtained by last-observation-carried-forward method. All statistical analyses will be performed by SPSS23 software (IBM, Chicago, IL), and *P* value <.5 will be considered statistically significant.

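### The adverse event definition requires causation while the collection rule does not; read literally, recorded events judged unrelated drop out of the safety comparison

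*Protocol article*

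**What the plan says.** Section 2.12 (Adverse event) opens with the definition: "Adverse events refer to the negative effects caused by the intervention". It then gives the collection rule, "During the trial, any abnormal reactions of the participants will be reported to the researchers", followed by "The time of onset, symptoms, degree, duration, and mitigation measures will be recorded in the CRF". Neither of these two sentences mentions cause, and relatedness is not among the items listed for the CRF.

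Section 2.11.4 (Safety outcomes) reads "Safety parameters include AEs and laboratory examinations (BR, LKF"), and section 2.14 (Planned statistical analysis) says "Safety, dietary quality, compliance indicators will be tested by" a chi-square or Fisher exact test. Section 2.9 (Emergency unblinding) keeps unblinded cases in an analysis that it names after adverse reactions rather than adverse events.

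On masking, section 2.8 says of the diet that "it is difficult to be blinded, so only drugs are double-blind to reduce information bias". The arms are given as: "A, B, and C are defined as Chinese medicine group, placebo + diet group, Chinese medicine + diet group". Section 2.7 (Intervention) has doctors complete the diet and stool diaries, receive each day's meals by phone message and press the diet patients to keep to the diet.

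**The concern.** The opening sentence of section 2.12 describes an adverse reaction, not an adverse event. Once cause is part of the definition, someone has to decide on cause before an event can be counted, and an event judged unrelated leaves both the safety outcome and the test between arms. The broader collection rule next to it does not say whether such events still count, so the article does not settle what the safety table contains.

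The Discussion gives clarifying the safety of both the diet and QJTCF as an aim of the trial. Randomisation protects a comparison of all events by arm. It does not protect a comparison of events filtered by a judgement whose basis differs between arms. Here the basis can differ, because knowing whether a patient is on the diet says something about the drug.

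**Working it through.** **1. The sentences side by side**

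| Place | What it governs | Condition on cause? |
|---|---|---|
| 2.12, first sentence | what an AE is | yes |
| 2.12, second sentence | what is reported | no |
| 2.12, third sentence | what the CRF records | no; relatedness not listed |
| 2.11.4 | AEs as a safety outcome | inherits the definition |
| 2.14 | test between arms | inherits the definition |

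Unrelated events may therefore reach the CRF and still not be AEs. The possible loss lies in counting, not necessarily in collection.

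**2. What diet status reveals about the drug**

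The planned sizes are 30 per arm (section 2.5). Group A has drug and no diet, B has placebo and diet, C has drug and diet.

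- P(active drug | no diet) = 30/30 = 1.0
- P(active drug | diet) = 30/(30 + 30) = 0.5

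Anyone who knows that a patient is not on the diet knows the whole of group A's treatment. Between B and C the drug stays masked while the blind holds.

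**3. Illustration of size**

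The article gives no AE rate and no attribution share, so there is no figure to reproduce and every rate here is an assumption. The true all-cause rate r is the same in both arms and n = 30. Attribution shares are q1 and q2. The count per arm is 30 × r × q. The last column is the exact probability that a two-sided Fisher test rejects at 0.05. That level is assumed, because section 2.14 prints .5.

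| r | q1 / q2 | Counted of 30 | Rejection |
|---|---|---|---|
| 10% | all counted | 3.0 / 3.0 | 0.9% |
| 10% | 80% / 50% | 2.4 / 1.5 | 0.7% |
| 10% | 80% / 40% | 2.4 / 1.2 | 1.0% |
| 10% | 90% / 20% | 2.7 / 0.6 | 2.8% |
| 20% | all counted | 6.0 / 6.0 | 2.2% |
| 20% | 80% / 50% | 4.8 / 3.0 | 3.9% |
| 20% | 80% / 40% | 4.8 / 2.4 | 6.1% |
| 20% | 90% / 20% | 5.4 / 1.2 | 21.2% |
| 40% | all counted | 12.0 / 12.0 | 2.6% |
| 40% | 80% / 50% | 9.6 / 6.0 | 11.9% |
| 40% | 80% / 40% | 9.6 / 4.8 | 21.3% |
| 40% | 90% / 20% | 10.8 / 2.4 | 67.5% |

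With equal arm sizes the rejection probability is unchanged when q1 and q2 are exchanged. Each row therefore covers higher attribution in A and, equally, higher attribution in B or C.

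The filter can also hide a difference. If the true rates were 40% and 20% with attribution of 40% and 80%, the counted rates would be 0.40 × 0.40 = 16% and 0.20 × 0.80 = 16%.

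Undercounting needs no gap between arms: at 50% attribution, half of all events go uncounted.

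**The case against.** The strongest reply is that the article describes no causality step. It names no assessor, no criteria and no rule that discards unrelated events, and it asks for "any abnormal reactions of the participants will be reported to the researchers" without qualification. Its safety vocabulary is loose throughout, so a causal phrase in one sentence does not prove that recorded events will be thrown away. This stands. A reader might infer that unrelated events will certainly be lost, but the text supports only that the definition excludes them and that the next sentences do not put them back.

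A second tempting inference is that group A will show too many AEs because its active drug is known. The documents do not support a direction. The diet is also an intervention and is openly known in B and C, and C receives both, so attribution there could match or exceed that in A.

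Other limits also stand. B versus C is protected for the drug while the blind holds. Blood routine and liver and kidney function do not depend on the definition. With mild differences in attribution the effect on the test is small: at a 20% rate and 80%/50% attribution, rejection is 3.9%, still below 5%, in a trial declared exploratory. The CRF is not shown and may already have a relatedness item.

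None of this removes the defect. The definition is written into the article and is not a detail left to a fuller document. It conflicts in scope with the collection rule beside it.

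**Conclusion.** The point holds as a badly fixed definition that carries a risk of bias. Read literally, section 2.12 excludes events judged unrelated from the safety outcome and from the test between arms, although such events may already be collected. The implied judgement would be made by staff who know diet status and hence know that group A is on active QJTCF.

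Undercounting is the more certain consequence if the definition is applied. Distortion of A versus B or A versus C is possible in either direction. Its size is unknown: over the assumed rates and attribution shares, false rejection runs from below 1% to 67.5%, and the high end needs both frequent events (40%) and a very wide attribution gap (90%/20%). These figures show sensitivity to the assumptions and do not predict this trial's results. The correction should be made because it is cheap and bears on a stated aim.

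**What to change.** Replace the first sentence of section 2.12 with a definition such as: an adverse event is any untoward medical occurrence from the start of intervention to the day-28 visit, whether or not it is considered related to the intervention. The definition then matches the collection rule that follows it.

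In section 2.14, make the comparison of all recorded, all-cause AEs by arm the main safety table. Report relatedness as a separate CRF item and in a secondary table, noting that those who judge it know diet status unless an assessor blinded to arm is used. Use one safety term throughout, including in section 2.9.

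The cost is a sentence in each section and one CRF item if the form lacks it. The small downside is that more events will be counted and reported.
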